### Study Population and Eligibility

#### Overview

Our study population consists of women in the premenopausal phase visiting the gynecological outpatient clinic with symptoms caused by uterine fibroids. Symptoms of fibroids may comprise heavy menstrual bleeding and bulk symptoms such as pelvic pressure, micturition/defecation problems, or pain symptoms. A combination of several symptoms or a single symptom will be equally qualified as “symptomatic.” To optimize external validity of our study results, the inclusion and exclusion criteria defined in this study (Textbox 1) are similar to the inclusion and exclusion criteria applied for MR-HIFU in clinical practice. However, 2 exceptions are made. Women need to be motivated to undergo 1 of the 3 treatments in the control group, in case of being randomized to the control group, before participating in the MYCHOICE study. Furthermore, a wish to conceive within 1 year after inclusion is a reason to be not eligible for participating, because there is not yet a consensus about the standard of care for these women. Women without an active child wish but for whom a pregnancy in the future is not ruled out can be included in the study.

The MYCHOICE study procedure consists of several steps (Figure 1).

The eligibility procedure for this study consists of 2 screening phases. Only women that are considered eligible for participating in the study based on these 2 screening phases will be randomized.

Inclusion criteria for participation in the MYCHOICE (MYoma treatment Comparison study: High-intensity image–guided fOcused ultrasound versus standard [minimally] Invasive fibroid care—a [Cost] Effectiveness analysis) study.

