#### Control Group

The care as usual group will be offered surgery or UAE. Surgery will be either hysterectomy or myomectomy. Both hysterectomies and myomectomies can be performed by laparoscopy or laparotomy depending on the size and location of the fibroids. Participants allocated to the control group can decide together with their gynecologist which of the (minimally) invasive treatments they wish to undergo. All of the usual care treatments are performed extensively at the participating centers and will be performed according to national guidelines and local protocols. Surgery is preceded by a preoperative screening for anesthetic risk assessment. Depending on the modus of the hysterectomy or myomectomy, patients will be hospitalized for a minimum of 1-3 nights. UAE will be performed by well-trained and experienced radiologists. UAE can be either unilateral or bilateral. The patient usually has to stay in the hospital for 1-3 nights for careful pain monitoring after the procedure. Six weeks after all usual care treatments, a follow-up appointment at the gynecology department will be scheduled.

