Patient-reported satisfaction with treatment and treatment preference (PREM^f^)	Because a randomized controlled trial will be performed, satisfaction with treatment might be affected by not being allocated to preferred treatment. Furthermore, we expect women declining participation because of the randomization aspect of the trial.	The PREM consists of a concise set of statements about the experience of the patients with the treatment and whether they would recommend the treatment to a friend. In addition, the preference will be registered for a particular treatment of potential participants before randomization. Women who decline participation in the study will also be asked if they are willing to disclose their reasons for declining.	The PREM score is scored on a 5-point Likert scale: higher score represents better experience. Whether there is a difference in PREM outcome between the 2 treatment arms is determined by linear regression analysis.
(Co)medication	Women (still) experiencing symptoms after treatment may take or may start to take medication to relieve these symptoms. Medication might also be used as contraceptive and to mask possible fibroid-related symptoms at the same time.	Data on any prescribed or over-the-counter medication taken to reduce fibroid symptoms as reported by the patient will be collected via the questionnaires at baseline, 3, 6, 12, and 24 months after treatment.	The number of women taking medication to suppress fibroid-related symptoms is measured at baseline and 3, 6, 12, and 24 months after treatment. The absolute numbers and percentage of women taking comedication per group per time point will be presented.
Reintervention rate and time to reintervention	A reintervention is defined as an additional intervention due to persisting or recurring symptoms of the treated fibroid or due to complications of the initial fibroid treatment.	Occurrence and type of reintervention are collected via both electronic patient file and questionnaires at 3-, 6-, 12-, and 24-month follow-up.	The reintervention rate at the follow-up time point of 24 months after MR-HIFU^g^ is presented as percentage reinterventions with its 95% CI. Reintervention rate will be presented per treatment arm but also per treatment. To investigate whether the time to reintervention differs between the 2 treatment arms, Cox proportional hazards analysis will be used.

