### Sample Size

The MYCHOICE study is a noninferiority trial for which we hypothesize that MR-HIFU is noninferior to the group of standard (minimally) invasive treatments, accepted by a ≤15 points difference in symptom reduction at 24 months’ follow-up as determined with the SSS (range 0-100 points) part of the UFS-QoL questionnaire. We expect that women participating in this trial have a slight preference for the noninvasive MR-HIFU treatment. We therefore choose to use an unbalanced design in which participants are allocated to the intervention or usual care group at a 2:1 ratio, resulting in a larger sample size in the MR-HIFU treatment group. With a larger sample size of the MR-HIFU treatment group, we will be able to gather more data on this new treatment while the effectiveness of standard care is already much better documented. Randomization, stratified by center, will be performed using a computer-generated randomization system, which randomly selects block sizes of 3, 6, or 9. Previous studies concerning (minimally) invasive treatments were performed with women with an average baseline UFS-QoL SSS of 55-65 points [33]. Treatment initiated a decrease of 30-47 points on SSS 12 months after these combined treatments. Hitherto, there are 2 MR-HIFU studies published that used a full ablation protocol, had the same 12-month follow-up period as the studies on (minimally) invasive treatments, and in which women participated with a baseline UFS-QoL SSS of 55-65 points. These women showed an SSS reduction of 30-40 points at follow-up [34,35]. In our study population we expect comparable baseline SSS in the MR-HIFU and standard care group. However, because hysterectomy results in a somewhat higher SSS reduction than the uterus-saving treatments, we assume in our power calculation an a priori 5-point delta between both the MR-HIFU and standard care group in favor of the standard care group. Using a noninferiority margin of 15 points with α (1-sided)=0.025, β=.1, and an SD of 20 points, we estimate that 192 participants (128 patients in the MR-HIFU treatment group and 64 patients in the [minimally] invasive treatment group) will be required to test noninferiority of MR-HIFU. Anticipating a 20% loss to follow-up, we need to include 160 patients in the MR-HIFU group and 80 patients in the (minimally) invasive treatment group. The noninferiority margin and the SD of 20 points were determined in consultation with the Dutch Society for Obstetrics and Gynecology and were similar to the noninferiority margin used in the MYOMEX-2 study [36].

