### Statistical Methods

In this study, data will initially be analyzed on an intention-to-treat-basis (including treatment failures) but a per-protocol analysis will also be performed. QoL at the follow-up time point of 24 months after treatment is determined as a change in SSS between baseline and 24 months’ follow-up. The difference between the symptom reduction after MR-HIFU and standard (minimally) invasive fibroid care including 97.5% CI is determined using linear regression analysis with a correction for baseline SSS. Although symptom reduction 24 months after MR-HIFU will be expected to be noninferior to standard (minimally) invasive fibroid care, the time course of symptom reduction may differ between the 2 treatment arms. This will be investigated with longitudinal covariance analysis. A faster symptom reduction in the usual care arm may be caused by a faster symptom reduction after hysterectomy. Therefore, a subgroup analysis in which the individual treatments are compared will be performed.

Patients can leave the study at any time for any reason if they wish to do so, without any consequences. In case they decide to withdraw before treatment or within the first 3-month follow-up, they will be included in the database, but an additional patient will be included to achieve the required sample size and reach primary outcome. In case patients withdraw after the 3-month follow-up, they are considered nonresponders. As much precautions as possible will be taken to prevent missing data. However, missing values are expected to occur in our trial due to technical failures and loss to follow-up. In case missing data reach 5%, additional analyzes will be performed to identify a plausible assumption, that is, missing not at random, missing at random, or missing completely at random. Subsequently, an analysis method that is valid under that assumption will be used.

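### The planned comparison of individual treatments rests on a choice made after randomization in one arm only, so it is confounded by choice; recording each woman's intended control treatment beforehand would allow a randomized version

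*Protocol article*

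**What the plan says.** In the Protocol article, Statistical Methods raises the possibility that usual care responds faster because of hysterectomy and then states: "Therefore, a subgroup analysis in which the individual treatments are compared will be performed". It does not say which women form the comparator, and it ties no adjustment to this analysis.

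Control Group explains how the individual treatment is set: "Participants allocated to the control group can decide together with their gynecologist which of the (minimally) invasive treatments they wish to undergo". The choice comes after allocation and exists in one arm only.

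Two other places touch on intention before randomization. The Overview under Study Population and Eligibility requires willingness: "Women need to be motivated to undergo 1 of the 3 treatments in the control group". Table 2 in Secondary Outcomes, in the row on satisfaction and preference, says that "the preference will be registered for a particular treatment of potential participants before randomization". Neither says that a named control option is recorded for each participant. Pretreatment places the collection of baseline data after the patient has been told her allocation.

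Limitations accepts that comparisons of individual treatments will suffer from low numbers. It does not mention that these comparisons are not randomized.

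**The concern.** Women who choose hysterectomy, myomectomy or UAE are likely to differ in ways that bear on outcome. The protocol gives one example itself: Limitations says that for women with a possible future pregnancy wish, myomectomy is the only alternative. Severity and fibroid characteristics may also steer the choice.

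The MR-HIFU arm contains women of all these kinds, unlabelled. A difference between one chosen treatment and MR-HIFU, or between two chosen treatments, therefore mixes the effect of treatment with the kind of woman who chose it. The reason given for the analysis is explanatory, namely whether hysterectomy drives a faster response, and a comparison by treatment received cannot answer that. Larger numbers would not cure it, so a limitation about sample size does not cover it.

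**Working it through.** **The plan's own figure.** Inputs from Sample Size: "Using a noninferiority margin of 15 points with α (1-sided)=0.025, β=.1, and an SD of 20 points"; "an a priori 5-point delta between both the MR-HIFU and standard care group in favor of the standard care group"; "participants are allocated to the intervention or usual care group at a 2:1 ratio".

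- Control n = (1 + 1/2) × [20 × (1.960 + 1.282) / (15 − 5)]² = 63.04, taken up to 64. MR-HIFU n = 128, total 192.
- With 20% loss: 64/0.8 = 80 and 128/0.8 = 160, total 240.

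This agrees with the protocol: "we estimate that 192 participants (128 patients in the MR-HIFU treatment group and 64 patients in the [minimally] invasive treatment group) will be required". No stated figure is in dispute, and 64 and 128 are used below as evaluable numbers.

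**Assumptions.** The protocol gives neither quantity, so both are varied.

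- p: the share of women who would choose a given control treatment, 0.1 to 0.6.
- d: the gap in expected SSS reduction between those women and all others under the same treatment, 5 to 10 points, with 15 as an extreme.

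**Bias of choosers against the whole MR-HIFU arm** (one possible comparator). Relative to the other women, choosers have mean d. The MR-HIFU arm has mean p × d, because a share p of it would have chosen the same. Bias = d − p × d = (1 − p) × d. At p = 1/3 this is 3.3 points for d = 5 and 6.7 points for d = 10.

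**Bias within a stratum of the same prerandomization intention.** Both arms have the same expected prognosis, so the bias is zero.

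**Precision**, with SD 20:

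- Whole arm: SE = 20 × √(1/(64p) + 1/128). At p = 1/3: 4.68.
- Same-intention stratum: SE = 20 × √(1/(64p) + 1/(128p)). At p = 1/3: 5.30.
- The ratio is √(1.5 / (1 + p/2)).

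| p | Women in stratum (control / MR-HIFU) | Bias, d = 5 | Bias, d = 10 | False-positive rate, d = 10 | 95% half-width, whole arm | 95% half-width, stratum | Ratio |
|---|---|---|---|---|---|---|---|
| 0.1 | 6.4 / 12.8 | 4.5 | 9.0 | 20% | 15.9 | 19.0 | 1.20 |
| 0.2 | 12.8 / 25.6 | 4.0 | 8.0 | 28% | 11.5 | 13.4 | 1.17 |
| 1/3 | 21.3 / 42.7 | 3.3 | 6.7 | 30% | 9.2 | 10.4 | 1.13 |
| 0.5 | 32 / 64 | 2.5 | 5.0 | 24% | 7.7 | 8.5 | 1.10 |
| 0.6 | 38.4 / 76.8 | 2.0 | 4.0 | 19% | 7.2 | 7.7 | 1.07 |

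The false-positive rate is the chance that the whole-arm contrast is significant at a nominal two-sided 5% when there is no treatment effect. With d = 5 it is 8% to 11%. With d = 15 the bias is 6.0 to 13.5 points and the rate is 37% to 57%.

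A simulation of 20,000 trials at p = 1/3, d = 10 and no treatment effect gave a mean difference of 6.7 points for the whole-arm contrast and 0.02 for the stratum contrast.

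**What the stratum contrast can decide.** With an estimated deficit of 5 points, the design assumption, the upper limit at p = 1/3 is 5 + 10.4 = 15.4, just beyond the 15-point margin. At p = 0.5 it is 5 + 8.5 = 13.5, inside it. At p = 0.2 it is 5 + 13.4 = 18.4.

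**The case against.** The strongest reply is that this is a secondary analysis of the time course. The protocol attaches no margin or noninferiority test to any subgroup, and the comparator and adjustment would normally be fixed in an analysis plan that is not shown. That is fair as to the comparator. It does not dispose of the point: the protocol states the analysis with a causal reason, and an analysis plan cannot later create a variable that had to be recorded before randomization in both arms.

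Three stronger readings are tempting and are not supported.

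- A reader might infer that each control treatment will be set against the whole MR-HIFU arm. Statistical Methods does not say so. The bias figures illustrate that one reading; comparisons among the control treatments are confounded as well.
- A reader might infer that the analysis is meant to resolve the mixed control group, or to show noninferiority for each kind of woman. The text ties it to a possibly faster response after hysterectomy. The mixed group is defended in Limitations as reflecting real-world care.
- A reader might infer that the preference item in Table 2 already supplies the strata. The recorded answer may be MR-HIFU itself, since Sample Size expects a slight preference for it and Recruitment notes that the trial is the only route to it. Its timing must also be reconciled with Pretreatment.

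Two further objections stand in part. The primary regression corrects for baseline SSS; carried into the subgroup, this would absorb some of a severity gap, but not a pregnancy wish or other reasons for choosing. The adjustment for comedication and menopause in Table 2 is not aimed at choice. And because Strengths expects most participants to prefer a uterus-preserving option, the hysterectomy stratum may be small.

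**Conclusion.** The point holds in a limited form. Treatment within the control arm is chosen after allocation, so comparing the individual treatments by what was received is confounded by choice, and the protocol neither names nor handles this. At an assumed one-third share and a gap of 5 to 10 points, the contrast with the whole MR-HIFU arm would be off by about 3.3 to 6.7 points before baseline adjustment, roughly 22% to 44% of the 15-point margin. Both the share and the gap are assumptions, so these figures show scale and do not predict the error.

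The primary randomized comparison, the margin and the sample size of 240 are untouched. This is a worthwhile improvement to a secondary analysis, not a flaw in the trial's main conclusion.

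**What to change.** 1. Before randomization, record for every woman which of the three control treatments she would have if allocated to standard care. Word the item so that MR-HIFU is not a possible answer. The answer need not bind the later choice.
2. State when the item is collected, and reconcile Table 2 with Pretreatment.
3. Compare the arms by intention to treat within the strata so defined, using an arm-by-intended-treatment interaction in the primary regression model.
4. Label comparisons by treatment received as descriptive.
5. Add confounding by choice to Limitations.

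The cost is one question and some wording, with no extra patients. Intervals are about 7% to 20% wider than in the whole-arm contrast. Strata may be small, about 6 against 13 women at a share of 0.1, and the hysterectomy stratum may not settle noninferiority. Stated intention may differ from treatment received, so each stratum compares MR-HIFU with standard care among women intending a given treatment, not with that treatment alone. Inclusion began in November 2020; women already randomized can contribute only if their recorded preference names a control option. Steps 4 and 5 are wording only and apply even if no new item can be added.

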### Data Collection

Data collection will take place before treatment, and at 3, 6, 12, and 24 months after treatment by questionnaires. Furthermore, baseline data of patient and treatment costs will be collected before treatment and after data lock-in (Table 1).

**Table 1 table1:** Timeline of data collection.

Data	Baseline	Treatment	3 months	6 months	12 months	24 months	Data lock-in
Informed consent	X						
Patient characteristics^a^	X						
Pregnancy outcomes^b^	X					X	
UFS-QoL^b,c^	X		X	X	X	X	
EQ-5D-5L^b,d^	X		X	X	X	X	
Onset of menopause^b^						X	
(Time to) reintervention^a^			X	X	X	X	X
Adverse events/complications^a^		X	X	X	X	X	
PREM^b,e^	X		X	X	X	X	
Recovery time^a^		X	X	X			
Medical Consumption Questionnaire^b,f^	X		X	X	X	X	
Productivity Costs Questionnaire^b,f^	X		X	X	X	X	
Costs of treatment^a^							X
Reason for not participating^a,g^	X						

^a^Retrieved from questionnaires and medical record.

^b^Retrieved from questionnaires solely.

^c^UFS-QoL: Uterine Fibroid Symptom and Quality of Life questionnaire.

^d^EQ-5D-5L: 5-level version of the EuroQoL Questionnaire.

^e^PREM: patient-reported experience measurement

^f^Used for the cost-effectiveness analysis.

^g^Data collected by the gynecologist in case of not willing to participate.

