
### Recruitment

In all participating hospitals, patients will be recruited during a visit at the gynecologist. Furthermore, a study website is created to inform patients from all over the country, providing information and contact details to directly contact the study team. By promoting this website among general practitioners, gynecologists, and potential participants, we expect women with an interest in MR-HIFU to become acquainted with our study. Because MR-HIFU treatment for uterine fibroids is not reimbursed in the Netherlands, participating in the MYCHOICE study is the only possibility for women to undergo MR-HIFU treatment.

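### The intention-to-treat label does not fit a rule that adds a patient for each early withdrawal and an endpoint dated from treatment: women who leave before treatment have no 24-month outcome

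*Protocol article*

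**What the plan says.** Statistical Methods states that "data will initially be analyzed on an intention-to-treat-basis (including treatment failures") and adds a per-protocol analysis. The primary comparison is a linear regression of the change in symptom severity score (SSS) from baseline to 24 months, adjusted for baseline SSS.

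The same section splits withdrawals by timing. For women who leave before treatment or within the first 3 months, "they will be included in the database, but an additional patient will be included to achieve the required sample size and reach primary outcome". Women who leave later are classed as nonresponders. Once missing data reach 5%, the missingness mechanism is to be examined and a method valid under it chosen.

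Data Collection fixes the clock: "Data collection will take place before treatment, and at 3, 6, 12, and 24 months after treatment by questionnaires". Recruitment notes that "participating in the MYCHOICE study is the only possibility for women to undergo MR-HIFU treatment".

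Sample Size already allows for attrition: "Anticipating a 20% loss to follow-up, we need to include 160 patients in the MR-HIFU group", with 80 in the control group.

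**The concern.** Intention-to-treat means that every randomized woman counts in the arm to which she was allocated. Two provisions work against that. The endpoint date depends on having been treated. And the additional patient is brought in expressly so that the primary outcome is reached, which suggests that the leaver is not expected to supply one. Keeping her in the database does not by itself put her in the regression.

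Early and late loss are also handled in opposite ways under one label. An early leaver prompts extra recruitment; a late leaver becomes a nonresponder, a term the article does not translate into a value on a continuous score.

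At stake is the noninferiority claim. The allocation is known to the woman, Sample Size expects participants to lean slightly toward MR-HIFU, and standard care exists outside the trial while MR-HIFU does not. A woman allocated to control therefore has less reason to stay than one allocated to MR-HIFU. If those who leave would have had different outcomes from those who stay, the observed contrast moves, and the documents do not show in which direction.

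**Working it through.** **1. Can an early leaver enter the stated analysis?** The regression needs a baseline SSS and a 24-month SSS. The second is defined at 24 months after treatment. For a woman never treated, that date does not exist, so her outcome is missing by construction. The Pretreatment section also places baseline data collection after the allocation is disclosed, so a woman who leaves on hearing her arm may lack the baseline score too. A woman treated but gone within 3 months has a date but no observation. Without imputation, both drop out.

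**2. The plan's own sample size.** Sample Size gives: "The MYCHOICE study is a noninferiority trial for which we hypothesize that MR-HIFU is noninferior to the group of standard (minimally) invasive treatments"; "Using a noninferiority margin of 15 points with α (1-sided)=0.025, β=.1, and an SD of 20 points"; and "we assume in our power calculation an a priori 5-point delta between both the MR-HIFU and standard care group in favor of the standard care" arm. The distance from the assumed truth to the margin is 15 − 5 = 10 points. With 2:1 allocation:

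- n(control) = (1.960 + 1.282)² × 20² × (1 + 1/2) / 10² = 63.04, rounded up to 64
- MR-HIFU 128, total 192
- Divided by 0.80: 80 + 160 = 240

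This matches the article. SE = 20 × √(1/64 + 1/128) = 3.062, and power = Φ(10/3.062 − 1.960) = 0.904.

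**3. Effect of selective loss (assumed inputs).** Let a share w of randomized controls be missing, and let their mean reduction differ by g points from that of controls who stay. The control mean then shifts by w × g. Assume no net shift in the MR-HIFU arm and no imputation. For a shift b at the planned 64 and 128:

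- error when the true difference equals the margin, shift favouring MR-HIFU: Φ(b/3.062 − 1.960)
- power at the assumed 5-point difference, shift against MR-HIFU: Φ((10 − b)/3.062 − 1.960)

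| w | g | b | One-sided error at margin | Power |
|---|---|---|---|---|
| – | – | 0 | 2.5% | 90.4% |
| 10% | 10 | 1 | 5.1% | 83.6% |
| 20% | 10 | 2 | 9.6% | 74.3% |
| 20% | 20 | 4 | 25.7% | 50.0% |

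Error and power are alternatives: one direction of shift inflates error, the other costs power.

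**4. Effect on numbers (assumed withdrawal rates).** The article does not say which arm an additional patient joins. The only allocation it describes is 2:1 in blocks, stratified by center. If additional women pass through that list until 240 remain:

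- N randomized = 240 / (1 − (2/3)w_h − (1/3)w_c), where w_h and w_c are the early withdrawal rates in the MR-HIFU and control arms
- Equal rates of 5%: N = 240/0.95 = 252.6; controls kept = 84.2 × 0.95 = 80.0, fully restored
- 5% MR-HIFU and 20% control: N = 240/0.90 = 266.7; controls kept = 88.9 × 0.80 = 71.1; MR-HIFU kept = 177.8 × 0.95 = 168.9

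After a further 20% loss, the second case leaves 56.9 and 135.1, with SE 3.161 and power 0.886. With no additional recruitment it would leave 80 × 0.80 × 0.80 = 51.2 and 160 × 0.95 × 0.80 = 121.6, with power 0.851. Adding women therefore helps power.

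With the SE of 3.161 from this depleted sample, the 2-point shift gives 9.2% error or 71.6% power, so the picture from step 3 is unchanged.

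**The case against.** The strongest reply is that no sentence removes early leavers from the analysis. They stay in the database, intention-to-treat is named as the initial analysis, and the 5% clause allows for data missing not at random. With 20% loss anticipated, that clause is likely to be triggered. A condensed article may also leave set definitions to the full protocol or analysis plan. This stands in part: exclusion is a likely consequence and not a written rule. It does not answer the main point, because the article does fix the endpoint clock and the purpose of the additional patient, and neither fits the label.

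Second, Study Population and Eligibility admits only women prepared to accept one of the control treatments, and Sample Size expects no more than a slight leaning toward MR-HIFU. Both reduce the risk of selective loss, so greater control withdrawal is plausible but not established.

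Third, the bias comes from missing outcomes and not from adding patients. It would be the same without the recruitment rule. This stands in full.

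A reader might infer that the rule swaps unwilling controls for willing ones, that control numbers are not restored, or that the randomized comparison is broken. The documents support none of these. Additional women have no described route in other than the same randomization, and they can withdraw too. Control numbers return to 80 when withdrawal is equal across arms. The article gives neither withdrawal rates nor any difference between leavers and stayers. The rule also concerns leaving the study, so a woman who declines her treatment but stays in follow-up does not trigger it.

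**Conclusion.** The point holds as an inconsistency between the intention-to-treat label, the treatment-dated endpoint and the handling of early withdrawals. As written, women who leave before treatment cannot contribute a 24-month SSS, and the analysed set drifts toward women who took up their arm.

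The size is unknown. A 2-point shift would take error at the margin from 2.5% to about 10%, or power from 90% to about 74%. That rests on three assumptions not found in the documents: 20% of controls missing, a 10-point gap from those who stay, and no offsetting shift in the MR-HIFU arm. The direction is also unknown. The shortfall in control numbers is secondary: about 71 of 80 kept and power about 0.89 in the 20% versus 5% example. The issue should be corrected because it touches the primary comparison and the repair is cheap.

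**What to change.** - Define the intention-to-treat set as all randomized women, including those who withdraw before treatment or within 3 months.
- Separate declining treatment from leaving the study. With consent, keep sending the existing questionnaires to women who decline treatment, on a schedule dated from randomization, so that a 24-month SSS exists for them.
- State the method for 24-month scores that remain missing, covering absent baseline scores and what nonresponder status means for a continuous outcome. Add a sensitivity analysis for outcomes missing not at random, with departures allowed to differ by arm.
- Keep additional recruitment if wanted, but describe it as extra randomized sample size under the same 2:1 allocation and not as replacement of leavers. Say how it relates to the 20% already built into 240.

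The cost is a short amendment and some additional questionnaire follow-up. Women who withdraw consent entirely will still have missing outcomes, so the sensitivity analysis remains necessary.

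### Late withdrawals are labelled nonresponders with no SSS value and also fall under a data-driven missing-data rule; if scored as zero change, the noninferiority error rate can move far from 2.5%, in a direction set by withdrawal in each arm

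*Protocol article*

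**What the plan says.** The Statistical Methods section of the Protocol article analyses the change in SSS from baseline to 24 months by linear regression adjusted for baseline SSS. Women who withdraw before treatment or in the first 3 months stay in the database and are replaced. For later withdrawals the rule is: "In case patients withdraw after the 3-month follow-up, they are considered nonresponders".

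The same paragraph then names loss to follow-up as a source of missing values. At a threshold of 5% missingness, the plan is that "additional analyzes will be performed to identify a plausible assumption, that is, missing not at random, missing at random, or missing completely at random"; a method valid under the chosen assumption is then applied.

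The Sample Size section sets the test: "Using a noninferiority margin of 15 points with α (1-sided)=0.025, β=.1, and an SD of 20 points", with an assumed "a priori 5-point delta between both the MR-HIFU and standard care group in favor of the standard care group". It requires "192 participants (128 patients in the MR-HIFU treatment group and 64 patients in the [minimally] invasive treatment group") and then inflates: "Anticipating a 20% loss to follow-up, we need to include 160 patients in the MR-HIFU group and 80 patients" in the standard care group.

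Table 1 shows the UFS-QoL, which contains the SSS, collected at baseline and at 3, 6, 12 and 24 months. Statistical Methods already plans a longitudinal covariance analysis for the time course of symptom reduction.

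**The concern.** Nonresponder belongs to a yes/no outcome. The primary endpoint here is a number, and the regression cannot use a woman until she has one. The article defines neither a responder nor an SSS value for a nonresponder, so the rule cannot be applied as printed.

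Three treatments of the same women sit side by side: nonresponder, missing value, and (in the sample size) no usable outcome. Nothing says which governs.

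The choice matters most in a noninferiority test. Giving the same fixed value to women in both arms can hide a real deficit. If withdrawal differs by arm, it can also create or remove a difference that has nothing to do with treatment effect.

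The missing-data rule does not settle the matter. Observed data can speak against MCAR but cannot distinguish MAR from MNAR. The 5% trigger corresponds to 0.05 × 240 = 12 women, while the planned loss is 240 − 192 = 48, so the rule should be expected to operate. As written, the method behind the confirmatory result depends on what the data look like.

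**Working it through.** **Inputs from the Sample Size section.** Margin 15, SD 20, one-sided α 0.025, power 90%, assumed difference 5, allocation 2:1, loss 20%, and a standard-care SSS reduction of 30–47 points at 12 months.

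**The plan's own figure.** Standard care: n = (1.960 + 1.282)² × 20² × (1 + 1/2) / (15 − 5)² = 10.51 × 6 ≈ 63.04, rounded up to 64. MR-HIFU is 2 × 64 = 128, total 192. For loss: 64/0.8 = 80 and 128/0.8 = 160, total 240. Both figures reproduce. With SE = 20 × √(1/64 + 1/128) = 3.06, power is Φ(10/3.06 − 1.96) = 90.4%. The inflation assumes that the 48 lost women contribute no outcome.

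**Assumptions needed to go further.** Nonresponder means zero change in SSS; withdrawal is unrelated to outcome; all 160 and 80 women are analysed. The base case is a standard-care reduction of 40 with MR-HIFU at 25, so the true deficit equals the margin.

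**Formulas.** With mean reduction m and late-withdrawal fraction d, an arm's analysed mean is (1 − d)m and its variance is (1 − d) × 20² + d(1 − d)m². The expected difference is therefore 15 + d_H × 25 − d_C × 40, where H is MR-HIFU and C is standard care. With equal d this is 15(1 − d).

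**Worked case, d = 20% in both arms.**
- Means: 0.8 × 40 = 32 and 0.8 × 25 = 20, difference 12.0.
- Variances: MR-HIFU 320 + 0.16 × 625 = 420; standard care 320 + 0.16 × 1600 = 576.
- Pooled variance: (159 × 420 + 79 × 576)/238 = 471.8, so the model's SE is √471.8 × √(1/160 + 1/80) = 2.97.
- Actual SE: √(420/160 + 576/80) = 3.13.
- False noninferiority: Φ((15 − 12 − 1.96 × 2.97)/3.13) = Φ(−0.90) = 18.3%.

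**All cases at a true 15-point deficit.**

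| Late withdrawal, MR-HIFU / standard care | Expected difference | False noninferiority, formula | Baseline-adjusted simulation |
|---|---|---|---|
| 5% / 5% | 14.25 | 4.8% | 5.8% |
| 10% / 10% | 13.5 | 8.1% | 8.9–9.4% |
| 20% / 20% | 12.0 | 18.3% | 19.2–19.9% |
| 10% / 20% | 9.5 | 46% | 49–51.5% |
| 20% / 10% | 16.0 | 1.3% | 1.4% |

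The simulations used 4,000 to 6,000 trials per case, with an assumed baseline SD of 15 or 18 and a baseline slope or correlation of 0.4.

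**Power.** With 20% / 10% and a true difference of 5 (40 against 35), the analysed difference is 0.9 × 40 − 0.8 × 35 = 8. Power is 62% by formula and 65% by simulation.

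**Break-even.** The mean does not shift when d_H × 25 = d_C × 40, for example 16% on MR-HIFU with 10% on standard care.

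**Range.** Over standard-care reductions of 30 to 47, the formula gives 17–21% at 20% / 20%, 37–51% at 10% / 20%, and 0.7–2.9% at 20% / 10%. The article does not say whether its 97.5% CI is one- or two-sided. If two-sided, the 20% / 20% base case gives 12% against a nominal 1.25%.

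**Comparison.** Leaving the missing values unimputed, with baseline adjustment and loss unrelated to outcome, gives a simulated error rate of 2.3–2.8%.

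**The case against.** The best defence is that nonresponder means only that no further questionnaires come back. The text gives this some support. SSS comes solely from questionnaires sent by email or post, the sentence contrasts with early withdrawals who are replaced, and the sample size removes lost women from the evaluable number. On that reading late withdrawals pass to the missing-data rule, nothing is set to zero, and none of the inflated rates arises. This stands as a possible reading, so zero change remains an assumption. It does not rescue the text, because the article never says which reading applies and the missing-data rule is still left open.

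Four stronger readings should be resisted:
- A reader might infer that the rule always favours noninferiority. It does not: with clearly more late withdrawal on MR-HIFU it is conservative and costs power. The open design and the expected preference for MR-HIFU make more withdrawal from standard care plausible, but the article gives no rates by arm.
- A reader might take 20% as the late-withdrawal rate. It is the total anticipated loss with no early/late split, and technical failures are listed separately, so results at 20% are an upper bound.
- A reader might conclude that the mechanism step is worthless. Data can count against MCAR, and plausibility can be argued from reasons for leaving. The limit is MAR against MNAR.
- A reader might infer that the method will be chosen with arm results in view. The article says neither when nor by whom it is chosen, and open describes treatment, not analyst access.

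An SAP may hold the detail, and leaving detail to it is no fault. The point here is what the article does state: two overlapping rules, one undefined for its endpoint and one data-dependent.

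**Conclusion.** The point holds in conditional form. The nonresponder label has no meaning for a continuous change in SSS, overlaps with the missing-data rule, and does not match the sample-size treatment of lost women.

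If it is applied as zero change, the error rate is no longer controlled at 2.5%. Equal late withdrawal of 5% or 10% takes it to about 5% or 9%, and 18–20% is the upper bound when all the planned loss is late. An imbalance of 10% on MR-HIFU against 20% on standard care takes it close to 50%. The reverse imbalance gives about 1%, with power of about 63% instead of the planned 90%. These sizes rest on zero change, withdrawal unrelated to outcome, and a standard-care reduction of 40 points.

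Independently of that reading, the confirmatory method is left to depend on the data through a step that cannot separate MAR from MNAR, under a trigger that the plan's own loss figure leads one to expect. Because the primary conclusion rests on these rules, they should be settled before any comparison by arm.

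**What to change.** 1. Delete the nonresponder rule for the SSS analysis, and delete the step that identifies the missingness mechanism from the data.
2. Fix in advance one primary analysis valid under MAR that uses SSS at 3, 6, 12 and 24 months with baseline adjustment. Either make the longitudinal covariance model already planned the primary model, with the 24-month contrast as the estimate, or use multiple imputation from the earlier visits feeding the planned 24-month regression. Either is sound; the text must name one.
3. Prespecify an arm-specific delta or tipping-point sensitivity analysis under MNAR that worsens missing MR-HIFU values in steps, for example up to the 15-point margin, and reports where noninferiority is lost.
4. Report late withdrawal by arm with reasons.

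The cost is a change of wording and a slightly more complex model than a single regression. The SSS visits are already scheduled, and the sample size stays at 192 evaluable and 240 randomized. The near-nominal error rate shown in the working is for complete cases under ignorable loss; the longitudinal model itself was not simulated.
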